A recent review [11] identified 12 studies in the period 1968–2009 reporting the effect of cigarette smoking on kidney allograft or recipient survival [14–25]. Although some of the revised studies showed contradictory results, in general cigarette smoking was associated with an increased risk of both graft loss and death. More recently, a large-scale study investigated the effect of smoking on post-kidney transplant outcomes in a retrospective cohort of 41,705 adult renal transplant recipients in the United States Renal Data System [26]. That work concluded that, compared with patients who have never smoked, new onset smoking after transplantation is associated with reduced allograft and patient survival. Similarly, a prospective study of 604 renal transplant recipients in The Netherlands showed that smoking after renal transplantation increases the risk of graft failure and mortality, while past smoking is a risk factor for mortality but not for graft failure [27]. Another European recent study in 402 randomly selected kidney graft recipients also concluded that smoking is a risk factor for kidney damage following renal transplantation [28].

Although there is evidence that active smoking plays an important role in allograft loss and patient mortality, this information has so far had little impact on patient management. Based on these results, smoking cessation should be promoted among patients undergoing kidney transplantation.

Both pharmacotherapy and non-pharmacological interventions could be used for the treatment of tobacco dependence. Non-pharmacological methods have the advantage of being inexpensive and feasible to implement, and may be particularly appropriate for transplant patients, who are usually polymedicated. The main non-pharmacological interventions for the treatment of tobacco dependence include advice from health professionals, self-help material, proactive telephone counseling, group or individual counseling, and intra-treatment or extra-treatment social support.

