### Inclusion criteria

Adult (over 18 years of age) kidney transplant recipients who smoke, with functioning allograft, who underwent primary or repeated renal transplantation from a cadaveric or a living donor in the A Coruña Hospital between 1981 and 2014Current daily smokers. Smoking status is defined according to the WHO classification. Therefore, a patient is considered a current daily smoker if they report daily smoking during the previous month, irrespective of the number of cigarettes smokedPatients in the precontemplation, contemplation or preparation stages, based on Prochaska and DiClemente’s transtheoretical model [33]

Smokers in the precontemplation stage have not seriously considered giving up smoking and do not think they will do so within the next 6 months. For the individual the pros of continuing smoking clearly outweigh the cons. They can be in this condition because they are misinformed or poorly informed about the consequences of their conduct or because they have tried to change it several times and are demoralized because they were not able to do so. They tend to avoid reading, speaking or thinking about the risk. Smokers in the contemplation stage have seriously considered giving up smoking within the next 6 months. They have not considered giving up smoking within the next 30 days or have not tried to stop for at least 24 h in the last year. They worry about the risks, their motivation to change or to remain without changing, and also their intention of changing in the long term, within the next 6 months but without specifying when. The smokers in the stage of preparation for the action have considered giving up smoking within the next 30 days, besides having made an attempt to abandon the habit for a duration of at least 24 h in the last year. Otherwise, they will be said to be in the stage of contemplation.

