### Intervention

At the baseline visit (visit 1) patients included in the study control group will be given a brief advisory session about giving up smoking. This will be firm, concise, personalized (trying to find the most important motivation for each patient) and appropriate to the phase towards cessation they are in. This will provide information about the negative effects of tobacco on their health and explain the main advantages of stopping smoking [36].

Patients included in the intervention group will receive the brief advisory session, as with the patients who belong to the control group, and in addition, CO-oximetry will be administered to them. This exploration allows one to know the amount of CO that the subject has in their body. The patient will take a deep breath and hold it for 15 s, then a slow, long and complete exhalation will be made. After a few seconds the oximeter indicator becomes stable and marks the exact number of particles per million (ppm) of CO that the subject has in the air they breathe. Follow-up visits will take place at 3 months (visit 2), 6 months (visit 3) and 9 months (visit 4). At each of these moments the anti-smoking advice will be repeated in the control group and anti-smoking advice plus CO-oximetry repeated in the intervention group (Table 2). At the 12-month (visit 5) visit, the anti-smoking advice will be given to both groups as well as CO-oximetry.

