Donor characteristics: age (years), gender and type of donor (deceased versus alive)Recipient features:Sociodemographic variables: age (years), genderChronic kidney disease-related risk factors: primary kidney disease, current treatment, previous transplants, cold ischemia timePre-transplant cardiovascular risk factors: weight (kg), height (m) and body mass index (kg/m^2^), basal cholesterol, systolic and diastolic pre-transplant blood pressure. Hypertension is defined as blood pressure above 140/90 mmHg. Pre-transplant hypercholesterolemia is considered as a cholesterol value above 200 mg/dl. Cardiovascular events before the transplant, tumors prior to transplant, smoking exposure prior to transplant, pre-transplant diabetes mellitus, and left ventricular hypertrophy will also be recordedPost-transplant cardiovascular risk factors: body mass index (kg/m^2^), systolic and diastolic blood pressure after transplantation, new appearance of diabetes mellitus after transplantation, left ventricular hypertrophy after transplantRoutine biochemistry on follow-up: creatinine (mg/dl), proteinuria (g/day), leukocyte count (number/l), hematocrit (%), hemoglobin (g/dl), serum albumen (g/dl), triglycerides (mg/dl), total cholesterol (mg/dl), HDL cholesterol (mg/dL), and LDL cholesterol (mg/dl)Transplantation outcomes in the follow-up: post-transplant cardiovascular events, acute rejection episodes, graft failure, and infectionsEvaluation of use of, and exposure, to tobacco:At the time of their incorporation in the study, the following information will be collected from all the patients:Self-reported smoking habit: number of cigarettes smoked per day and number of years of being smoker (the pack-years index will be computed)Number of previous attempts to stop smokingMaximum period of time elapsed without smokingConsumption of tobacco between their family and/or circle of friendsBoth at baseline and during follow-up at 3, 6, 9 and 12 months, the following information will be collected from each patient:Self-reported use of tobacco and number of cigarettes smoked per dayUrinary cotinine testStage of change, according to the Prochaska and DiClemente’s Stages of Change model (precontemplation, contemplation, preparation, abandonment) [33]Nicotine dependence measured by the Fagerström test [35]. This test is used to evaluate the degree of physical dependence on nicotine. It consists of six items with two or four possible answers. The score ranges from 0 to 10. The cutoff points are 4 and 7, where less than 4 means a low dependence, between 4 and 7 means a moderate dependence, and over 7 means high dependenceMotivation for giving up smoking, measured by the Richmond test [34]. This is a test that has four items with two or four possible answers. The score range is between 0 and 10, where item 1 rates between 0 and 1 and the other items range from 0 to 3.Based on this score, patients can be classified, according to their motivation for giving up smoking, in four groups: nil or low (0–3 points), doubtful (4–5 points), moderate (6–7 points), or high (8–10 points)

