### Outcome assessment

The effectiveness of both interventions will be evaluated at 3, 6, 9 and 12 months after inclusion in the study. The following outcomes will be investigated (Table 2):

**Table 2 Tab2:** Interventions and measurements in the follow-up after randomization

	Basal	3 months	6 months	9 months	12 months
Group allocation and intervention					
, Control group:					
Brief advice on smoking cessation	x	x	x	x	x
, Intervention group:					
Brief advice on smoking cessation + CO-oximetry	x	x	x	x	x
Outcome assessment					
Pattern of tobacco use (self-reported tobacco use)	x	x	x	x	x
Smoking cessation rates		x	x	x	x
Carbon monoxide (CO) levels in exhaled air by CO-oximetry in the intervention group	x	x	x	x	x
Carbon monoxide (CO) levels in exhaled air by CO-oximetry in the control group					x
Urinary cotinine tests	x	x	x	x	x
Nicotine dependence (Fagerström test scores)	x	x	x	x	x
Motivational stages of change (Prochaska and DiClemente’s stages)	x	x	x	x	x
Motivation for giving up smoking (Richmond test scores)	x	x	x	x	x

Smoking habit cessation, confirmed by a urinary cotinine test. The intervention will be considered effective if the test results are lower than 100 ng/mlSelf-declared abandonment of smoking habitReduction in the number of cigarettes smoked per day self-declared by the patientVariation in the motivational stage of change, according to the Prochaska and DiClemente’s Stages of Change model [33]Change in motivation to giving up smoking, according to the Richmond test [34]Change in nicotine dependence, measured according to the Fagerström test [35]

In the intervention group, the variation in CO levels in exhaled air, measured by CO-oximetry, will be registered. Main outcome will be mean urinary cotinine test differences between the two groups at 12 months. Secondary outcomes will include: urinary cotinine test results at 3, 6 and 9 months, CO-level differences at 12 months, as well as differences in self-reported tobacco use, nicotine dependence, Prochaska and DiClemente’s motivational stages of change and the Richmond test scores at 3, 6, 9 and 12 months of follow-up.

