### Statistical analysis

Comparability of intervention and control groups will be checked in terms of the similarity of the distribution of the variables of interest at baseline. The response that patients rate, at different time points in the follow-up, will be compared in both arms of the study according to the outcomes studied.

The chi-square test or Fisher’s exact test will be used to compare proportions. Student’s *t* test will be used to compare means between groups with a normal distribution data. The Mann-Whitney test will be used to compare quantitative variables between groups in case of a non-normal distribution, determined by the Kolmogorov-Smirnov test.

Correlations between quantitative measurements will be determined by the Spearman’s rho correlation coefficient. Matched-pair data analysis will be also computed. Therefore, to evaluate the differences within each group at different time points, McNemar’s test and Wilcoxon’s signed ranks test will be calculated.

Additionally, clinical relevance from intervention will be studied by calculating the relative risk (RR), relative risk reduction (RRR), absolute risk reduction (ARR) and patient number needed to treat (NNT) at different times during the follow-up. All these measures will be presented with their confidence interval at 95 %.

A multivariate analysis using multiple linear regression and logistic regression will be performed, according to the considered response, to adjust the effectiveness of the intervention as potential confounders and to determine which other variables are associated with each of the results. Variables with statistical significance *p* <0.10 in the bivariate analysis will be selected to be included in the multivariate regression analysis. A modeling strategy of successive steps back will be used.

The degree of agreement between the self-declared smoking consumption, CO-oximetry results and the test results of urinary cotinine levels at 3, 6, 9 and 12 months after surgery will be evaluated. The agreement will be evaluated by the kappa index.

The validity of self-declared smoking consumption by patients regarding the results of the CO-oximetry and urinary cotinine test will be studied. Sensitivity, specificity and positive and negative predictive values will be determined, together with their 95 % confidence interval.

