Moreover, on the other hand this study will determine the correlation between self-reported exposure and cotinine findings using a urine test strip as well as those from CO-oximetry. Although CO measurement is not the best indicator of smoking cessation, at least for occasional smokers, due to its short half-life, the use of different outcome measures at different moments of time will allow us to see the consistency of the results among them.

Finally, if effectiveness of CO-oximetry is confirmed to reduce tobacco exposure in this subset of patients, we would have an intervention that is easy to use, economic and with considerable implications for cardiovascular risk prevention.

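### Urinary cotinine, the main outcome and the cessation test, has no stated correction for urine dilution or graft function, and creatinine is adjusted for only if data-driven selection keeps it

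*Protocol article*

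**What the plan says.** The Outcome assessment section defines the main outcome: "Main outcome will be mean urinary cotinine test differences between the two groups at 12 months". The same section sets the biochemical confirmation of cessation at a urinary cotinine below 100 ng/ml. It mentions no creatinine ratio, specific gravity or timed collection.

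The Inclusion criteria admit "Adult (over 18 years of age) kidney transplant recipients who smoke, with functioning allograft", with transplants performed between 1981 and 2014. Table 1 ticks routine biochemistry at baseline and at 3, 6, 9 and 12 months, and the list in Independent measures opens with "creatinine (mg/dl), proteinuria (g/day), leukocyte count (number/l". The specimen is not named; the context reads as serum.

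The Statistical analysis section compares quantitative outcomes by Student's t test ("test will be used to compare means between groups with a normal distribution data") or by Mann-Whitney when the distribution is not normal. For the regression models, variables with p<0.10 in bivariate analysis "will be selected to be included in the multivariate regression analysis", followed by backward elimination. Creatinine has no named role.

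The Discussion refers to "cotinine findings using a urine test strip as well as those from CO-oximetry".

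**The concern.** A result in ng/ml is mass per volume of urine. The same excreted cotinine in twice the urine reads half as high, so a value can move, and can cross a fixed cutoff, with no change in smoking. Grafts up to three decades old are likely to differ in function, so renal handling is a plausible further source of spread between patients.

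The Statistical analysis section does fix a covariate rule, and that rule lets the sample decide whether renal function is adjusted for. The adjusted model for the main outcome is therefore unknown until the data are seen, although a relevant baseline measure is already being collected. At stake are the precision of the main comparison and some attenuation of the cessation difference, and of the absolute risk reduction and number needed to treat derived from it. The planned sensitivity and specificity of self-report are also affected, because urinary cotinine is one of their reference tests.

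**Working it through.** **The plan's own figure.** The Sample size section gives 56 per arm for a 13-point difference over 5–6 %, with 80 % power, two-sided 5 % and 10 % loss. The pooled two-proportion formula gives 94 (5 % v 18 %) to 101 (6 % v 19 %) evaluable patients per arm. With 56 × 0.9 ≈ 50 evaluable per arm, power is 50–53 %. That mismatch is a separate matter; it enters here only as the starting point of illustration B. The document gives no SD or expected difference for cotinine, so no planned power exists for the main outcome.

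**Cutoff arithmetic.** Reading = undiluted concentration ÷ dilution factor. A smoker at 150 ng/ml reads 150 ÷ 1.5 = 100, so any dilution beyond 1.5-fold brings the reading under the cutoff.

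**Illustration A: noise in the mean comparison (assumed inputs, log scale).** Let between-patient log-SD from smoking exposure be 1.0, and suppose 50 per arm gives 80 % power on that scale.
- Detectable standardised difference: (1.960 + 0.842) × √(2/50) = 0.560.
- Independent dilution and renal variation with log-SD d raises the SD to √(1 + d²).
- Power = Φ(0.560 / √(1 + d²) × √25 − 1.960).

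| d (assumed) | SD | Power |
|---|---|---|
| 0 | 1.000 | 80 % |
| 0.3 | 1.044 | 76.5 % |
| 0.5 | 1.118 | 71 % |
| 0.7 | 1.221 | 63 % |

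**Illustration B: misreading at the cutoff.** Take true cessation of 5 % v 18 %, and let a share f of continuing smokers in both arms be counted as quitters. Each observed rate is p + (1 − p)f, so the difference is 0.13 × (1 − f).

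| f (assumed) | Observed rates | Difference (points) | Power, 50 per arm |
|---|---|---|---|
| 0 | 5.0 % v 18.0 % | 13.0 | 53 % |
| 2 % | 6.9 % v 19.6 % | 12.7 | 47 % |
| 5 % | 9.8 % v 22.1 % | 12.35 | 39 % |
| 10 % | 14.5 % v 26.2 % | 11.7 | 30 % |

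Most of the power loss in B comes from the higher base rate, since the difference itself shrinks little.

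**What the covariate can do.** Adjusting for baseline creatinine multiplies the residual variance by (1 − r²), where r is its correlation with 12-month cotinine within arm. The document gives no r. The covariate can absorb stable differences in graft function. It cannot correct the dilution of one urine sample taken a year later.

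**The case against.** The strongest reply is that the article is condensed. The unit, assay and any correction for the main outcome could stand in a laboratory manual, the full protocol or an analysis plan. That stands for the mean outcome, where an uncorrected concentration is inferred from silence. It does not cover the cutoff, which is printed in ng/ml, or the covariate rule, which is printed in full.

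Three stronger readings are tempting, and the document supports none of them.

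- *Dilution biases the trial.* Nothing suggests that dilution or graft function differs by arm, and randomisation should balance both.
- *Any diluted smoker counts as a success.* The Background and Outcome assessment sections speak of cessation confirmed by cotinine. This can be read as needing a reported quit as well as a low value. On that reading an error needs both a dilute sample and a false report, and f in illustration B would be smaller.
- *Graft failure removes the main outcome selectively among smokers.* The Background does cite evidence that "smoking after renal transplantation increases the risk of graft failure and mortality". It gives no 12-month failure rate, such patients may still pass urine, the sample size already allows 10 % loss, and handling of these events is commonly left to an analysis plan.

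There is also a partial safeguard: at 12 months "the anti-smoking advice will be given to both groups as well as CO-oximetry", so a marker independent of urine exists in both arms, and agreement between the measures is planned.

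Finally, if the strip returns a band and not a number, illustration A does not apply and a creatinine ratio cannot be formed. That objection is sound and limits the second part of the fix.

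**Conclusion.** The point holds in a limited form. The cutoff is an uncorrected concentration, the main outcome has no stated correction, and adjustment for renal function is left to p<0.10 screening with backward elimination. The expected consequence is lower power and a somewhat attenuated effect, without systematic bias between arms.

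The size cannot be taken from the document. The power range of 76.5 to 63 % and the difference of 12.7 to 11.7 points rest on the assumed values of d and f, and A also assumes a quantitative assay analysed on the log scale, whereas the plan compares means or ranks. Quitters widen the spread of cotinine within an arm, so dilution is a smaller share of total variance than a calculation among smokers alone would suggest. This is an improvement worth making to a stated rule; it does not invalidate the design.

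**What to change.** 1. In the Statistical analysis section, name baseline serum creatinine as a fixed covariate in the 12-month cotinine comparison, exempt from the p<0.10 screen and backward elimination. It is already collected, so the cost is wording only. State that this addresses graft function and not the dilution of a single sample.
2. State whether cotinine values are corrected for dilution, and reconcile the test strip in the Discussion with a mean outcome and a cutoff in ng/ml.
3. If the assay is quantitative, prespecify a supporting analysis of cotinine per mg urine creatinine, reported beside the uncorrected result. The cost is one inexpensive urine creatinine measurement per sample. Urine creatinine also varies with muscle mass, which is why the ratio should accompany the uncorrected result and not replace it.

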### Statistical analysis

Comparability of intervention and control groups will be checked in terms of the similarity of the distribution of the variables of interest at baseline. The response that patients rate, at different time points in the follow-up, will be compared in both arms of the study according to the outcomes studied.

The chi-square test or Fisher’s exact test will be used to compare proportions. Student’s *t* test will be used to compare means between groups with a normal distribution data. The Mann-Whitney test will be used to compare quantitative variables between groups in case of a non-normal distribution, determined by the Kolmogorov-Smirnov test.

Correlations between quantitative measurements will be determined by the Spearman’s rho correlation coefficient. Matched-pair data analysis will be also computed. Therefore, to evaluate the differences within each group at different time points, McNemar’s test and Wilcoxon’s signed ranks test will be calculated.

Additionally, clinical relevance from intervention will be studied by calculating the relative risk (RR), relative risk reduction (RRR), absolute risk reduction (ARR) and patient number needed to treat (NNT) at different times during the follow-up. All these measures will be presented with their confidence interval at 95 %.

A multivariate analysis using multiple linear regression and logistic regression will be performed, according to the considered response, to adjust the effectiveness of the intervention as potential confounders and to determine which other variables are associated with each of the results. Variables with statistical significance *p* <0.10 in the bivariate analysis will be selected to be included in the multivariate regression analysis. A modeling strategy of successive steps back will be used.

The degree of agreement between the self-declared smoking consumption, CO-oximetry results and the test results of urinary cotinine levels at 3, 6, 9 and 12 months after surgery will be evaluated. The agreement will be evaluated by the kappa index.

The validity of self-declared smoking consumption by patients regarding the results of the CO-oximetry and urinary cotinine test will be studied. Sensitivity, specificity and positive and negative predictive values will be determined, together with their 95 % confidence interval.

All analyses will be performed by intention-to-treat, in which the total value of randomization will be preserved and control over confounding reference will be also ensured. Analyses will be performed using the statistical package Statistical Package for the Social Sciences software, version 19.0 (SPSS, Chicago, IL, USA).

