### Sample size

Meta-analyses have shown that around 5–6 % of smokers stop after the brief advisory session from a physician [36]. A 13 % increase in the cessation rate for the brief advisory session plus CO-oximetry over the brief advisory session alone is considered clinically relevant. The sample target size is, therefore, 112 patients, with 56 patients in each group of the trial. Allowing for up to 10 % loss to follow-up, this would provide 80 % power to detect a 13 % difference in smoking cessation outcomes at a two-tailed significance level of 5 %.

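### The regression that adjusts the treatment effect selects covariates by their p-values in the trial data, does not state that treatment stays in or that candidates are baseline only, and also serves to find predictors

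*Protocol article*

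**What the plan says.** In the protocol article, Statistical analysis, the multivariable models have two aims: "to adjust the effectiveness of the intervention as potential confounders and to determine which other variables are associated with each of the results". Covariates are chosen in two steps, a screen at p<0.10 followed by backward elimination: "bivariate analysis will be selected to be included in the multivariate regression analysis. A modeling strategy of successive steps back will be used". No list of candidate variables is given, no removal threshold, no statement that the treatment term is retained and no restriction to baseline values. The abstract names linear and logistic multiple regression, after descriptive statistics, as the analysis.

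Under Independent measures, Table 1 and the text list donor, recipient and pre-transplant variables. They also list follow-up blood pressure, body mass index, new-onset diabetes, biochemistry, cardiovascular events, rejection, graft failure and infections. For tobacco use, cotinine, stage of change, dependence and motivation, the text says that both at baseline and "during follow-up at 3, 6, 9 and 12 months, the following information will be collected from each patient".

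Outcome assessment makes mean urinary cotinine at 12 months the main outcome. Statistical analysis separately plans direct comparisons between arms, and relative risk, relative and absolute risk reduction and number needed to treat with 95 % confidence intervals.

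**The concern.** Randomisation already removes confounding on average. Covariates in a trial model serve to gain precision, and that works best when they are few, prognostic and fixed beforehand. Here the same outcome data choose the adjustment set and then estimate the effect. The reported standard error ignores the choice, and the final covariates are unknown until the data are seen.

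Two silences could make this worse. If the treatment term is screened and eliminated like any other variable, an adjusted effect exists only when it happens to be large. If follow-up smoking or motivation measures are candidates, a p<0.10 screen will favour them, because they correlate with 12-month cotinine and cessation. Adjusting for them would remove part of the effect being estimated. Predictor-finding tolerates data-driven selection, but estimating a randomised effect does not need it.

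**Working it through.** The plan gives no figure of its own for this point, so the check uses its sample size inputs.

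**Inputs (Sample size section).** Control cessation: "around 5–6 % of smokers stop after the brief advisory session from a physician", midpoint 5.5 %. Effect: 13 percentage points (absolute reading assumed), hence 18.5 %. Size: "112 patients, with 56 patients in each group of the trial". Loss: "Allowing for up to 10 % loss to follow-up", so about 56 × 0.9 ≈ 50 evaluable per arm.

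**1. Expected quitters (logistic model only).** Quitters = n per arm × (p1 + p2).
- 50 per arm: 50 × (0.055 + 0.185) = 12.0. Range 50 × 0.23 = 11.5 to 50 × 0.25 = 12.5.
- 56 per arm: 56 × 0.24 = 13.4. Range 56 × 0.23 = 12.9 to 56 × 0.25 = 14.0.
- About 45 baseline candidates can be counted under Independent measures, so 12 / 45 ≈ 0.3 quitters per candidate before screening.

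**2. Linear model, treatment kept in, baseline noise only.** Assumptions: 50 per arm, 30 independent noise covariates, screen at p<0.10, backward removal at p>0.10, 2,000 trials. True effects of 0, 0.3 and 0.5 SD gave mean estimates of 0.00, 0.29 and 0.48 SD. Coverage of the 95 % interval was 93.6–93.9 %, and type I error was 6.5 %. About 2.1–2.3 noise variables stayed in. A rerun agreed: coverage 93.7–94.4 %.

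**3. Logistic model, treatment kept in.** True odds ratio = (0.185/0.815) / (0.055/0.945) = 3.9. With selection among 30 noise covariates, the median adjusted odds ratio was 4.5 (300 trials), 4.8 (600 trials) and 4.9 (1,000 trials). In the 1,000-trial run the unadjusted fit on the same data gave 4.3. So part of the excess over 3.9 is ordinary small-sample bias with few events, and selection adds the rest. Interval coverage stayed at about 95–98 %.

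**4. If treatment had to pass the screen.**
- Cessation: summing the two binomial distributions over all outcomes in which the uncorrected chi-square gives p≥0.10 (50 per arm, 5.5 % against 18.5 %) gives 0.340. With 56 per arm it is 0.30. As a cross-check, normal-approximation power at the two-sided 10 % level with 50 per arm is 0.642, and 1 − 0.642 = 0.358.
- Full screen plus elimination, logistic: treatment was lost in 48–52 % of 800 replicates (30 or 45 candidates, Wald tests). Where it stayed, the median log odds ratio was 2.0–2.2 against a true 1.36.
- Linear, true effect 0.3 SD: treatment was lost in about 62 % of trials. Where it stayed, the mean estimate was 0.48 SD, and 0.48 / 0.3 = 1.6, or 60 % too large.

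**5. If a follow-up mediator entered.** Illustration: treatment shifts a follow-up measure by 0.5, that measure shifts the outcome by 0.5 per unit, and the direct effect is 0.25. The total effect is 0.25 + 0.5 × 0.5 = 0.50. After adjusting for the measure, 0.25 remains. The simulation gave 0.50 and 0.25.

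**The case against.** The strongest reply has four parts.

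First, a model whose purpose is to adjust the intervention effect must contain the intervention, and the reference to other variables implies that treatment is already there. A reader might infer that treatment will be screened and often dropped. The text does not say so. It only fails to exempt treatment, and the stated aim favours retention. The figures in step 4 are therefore conditional.

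Second, Independent measures lists what is recorded, not what is modelled. The adjusters are called potential confounders, and the repeated tobacco and motivation measures are named as outcomes. A reader might infer that the plan adjusts for follow-up measures. The documents support only that these are not excluded.

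Third, a reader might conclude that the adjusted estimate and its interval are invalid, or that a dozen quitters undermine the main analysis. Neither follows. The main outcome is continuous, so the quitter count concerns only the logistic model. With treatment kept and baseline candidates, the linear harm is small, and logistic coverage does not fall below nominal. The ratio of 0.3 quitters per candidate also counts variables before screening. About 3–4 unrelated variables pass the screen.

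Fourth, the direct comparisons and the risk measures do not use the selection rule, so an effect estimate is reported whatever the regression does.

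All four points stand as limits. They do not remove the central point: the article itself fixes outcome-driven selection for the adjusted effect, so this is not a detail left to a fuller plan. Nothing it says confines the rule to the benign case.

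**Conclusion.** The concern holds in limited form. The plan fixes p-value selection and backward elimination for the regression that adjusts the randomised effect, and merges that task with predictor-finding. It states neither that treatment is retained nor that candidates are baseline only.

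The size depends on the reading. On the benign one, the cotinine model loses about 1–1.5 points of coverage and is slightly attenuated. The cessation model overstates the odds ratio, with a median of 4.5–4.9 against a true 3.9, part of which comes from small numbers rather than selection. On the less likely reading that treatment is screened, it fails p<0.10 in about 34 % of trials under the planned cessation effect. A 0.3 SD effect is then lost in about 62 % of trials and averages 0.48 SD when kept. If follow-up smoking or motivation measures entered, part of the effect would be removed.

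These figures assume 50 evaluable per arm, independent noise covariates, 30 candidates unless stated otherwise and removal at 0.10. The protocol gives neither the candidate count nor the removal threshold. The change is worth making, but the planned unadjusted results are not in question.

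**What to change.** Separate the two aims.

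(a) **Adjusted treatment effect.** Fix the model before outcome data are examined by arm. Force treatment in. Include the baseline value of the outcome where one exists, for example baseline urinary cotinine for the main outcome. Add at most one or two prespecified baseline prognostic variables already collected, such as the Fagerström score or stage of change. Use no p-value selection and no post-randomisation covariates. For cessation there is no baseline value, since all participants smoke at entry. With about 12 quitters, a single score costs one parameter, whereas the three eligible stages cost two.

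(b) **Predictors.** If the p<0.10 screen and backward steps are kept, confine them to a separate analysis labelled exploratory.

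In simulation, treatment forced in with one prespecified covariate gave mean linear estimates of 0.29 and 0.49 SD for true effects of 0.3 and 0.5 SD. For cessation the median log odds ratio was 1.41–1.50 against a true 1.36, with about 97 % coverage. The remaining small-sample excess could be reduced by Firth-penalised logistic regression, which is optional.

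The cost is analysis-plan wording and minor analysis work. A Firth fit may need an extension to SPSS 19 or other software. No new data are needed.
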